**Provisional sample size calculation agreed with the funder following the start of the COVID pandemic:**

To detect a 1-day difference among individuals having an infection (hazard ratio 1.2) for alpha of 0.01 and 90% power, we estimated we would require 147 individuals per group, and allowing for at least 15% of individuals to contract an infection during a 6-month winter/spring period 980 individuals per group. With four groups and 80% follow-up, then 4900 individuals would be needed. We also aim to estimate outcomes in the three strata (stratum 1 –recurrence, no risk factors; stratum 2—risk factors, no recurrence; stratum 3—risk factors plus recurrence) so planned to recruit 14,700 participants in total. We accepted that this would provide less power for our key secondary outcome (incidence of infections). However, the aim for the latter outcome is to compare each intervention with control, so using the arguments of Cook and Farewell, since each analysis of intervention versus control is independent, this should not require a conservative Bonferroni correction [28], and we can use an alpha of 0.05. Using these assumptions, the above sample size would provide more than 80% power to estimate a 25% reduction in the incidence of infections from 20% to 15% in each stratum and more than 90% power if the incidence of infections is 15% using all strata combined. We will update the sample size calculations based on the observed rates of infections in each season when the SAP is drafted.

**Revised estimates for the primary outcome based on data of the incidence of infections from the first two seasons (2020/21; 2021/22):**

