Stratum 1 (recurrence, no risk factors): Currently, in this group about 71%, compared to our original assumption of 15%, had an infection. Basing our recalculation on the more conservative lower limit of the 95% confidence interval of this estimate, we might assume that at least 65% of this group get an infection. Based on the original number per group of 147 (i.e. changing no other assumptions), we’d need 226 per group, and for 4 groups and with 80% follow up 1130. For 80% power, based on the original assumptions, we would require 111 per group. If 65% get an infection, then we would need 111/0.65 = 171 per group. For 4 groups with 80% follow up we would require 855 participants.Stratum 2 (risk factors, no recurrence): In this group, the observed infection rate has been around 40% compared to our assumption of 15%. On this basis, based on the original sample size calculation of 147 per group, we would require 147/0.40 = 368 per group. With 4 groups and 80% follow up this gives a total of 1472 for 90% power. For 80% power, we would require 1388 participants.Stratum 3 (risk factors plus recurrence): The infection rate is currently around 62% and follow up is just under 80%. On the basis of the original calculation, assuming at least 60% having an infection, we would need 245 per group, time 4 groups with 80% follow up gives 1225.

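### Section 2.6: a hazard ratio of 1.2, alpha 0.01, 90% power and 147 infected people per group cannot all hold, and the revised primary-outcome sizes inherit the inconsistency

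*Protocol article*

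**What the plan says.** The provisional calculation in section 2.6 describes the target effect in two ways at once: "To detect a 1-day difference among individuals having an infection (hazard ratio 1.2", the hazard ratio standing in brackets after the difference in days. The operating characteristics and the result follow in the same sentence: "hazard ratio 1.2) for alpha of 0.01 and 90% power, we estimated we would require 147 individuals per group". This is then inflated for the share expected to be infected ("allowing for at least 15% of individuals to contract an infection during a 6-month winter/spring period 980 individuals per group") and for loss to follow-up ("With four groups and 80% follow-up, then 4900 individuals would be needed"). Three strata of that size give the planned 14,700.

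The revised estimates update the infection rate from the first two seasons and keep the rest. For stratum 1 the text says "Based on the original number per group of 147 (i.e. changing no other assumptions", giving 226 per group and 1130 in total; an 80%-power variant uses 111 infected per group, giving 171 and 855. For stratum 2 it says "based on the original sample size calculation of 147 per group, we would require 147/0.40 = 368 per group", with a total of 1472, or 1388 for 80% power. Stratum 3 gets 245 per group and 1225 in total.

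No SD, duration distribution or sidedness of the test is stated.

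**The concern.** An HR of 1.2 is a small effect, and 147 events per group is few for it at an alpha as strict as 0.01. The mismatch sits within a single sentence, so it is not a matter of detail left to the analysis plan. The revision changes only the infection rate, so any fault in 147 passes unchanged into the later primary-outcome figures.

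At stake is how stratum results will be read. If a stratum is believed to have 80% or 90% power for the stated effect and in fact has far less, a null result there would be taken as evidence of no benefit when it is largely uninformative.

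**Working it through.** **Inputs from section 2.6:** HR 1.2; alpha 0.01; power 90% (147 infected per group) or 80% (111); infection rates 15% originally, then 65%, 40% and 60% for strata 1, 2 and 3; four equal groups; 80% follow-up.

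**Assumptions of this check:** two-sided test of one group against another; every infected person contributes one event (recovery), which is the most favourable case.

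**1. The plan's arithmetic after 147.** 147/0.15 = 980; 980 × 4/0.8 = 4900; 147/0.65 = 226; 147/0.40 = 368; 147/0.60 = 245. These reproduce. (The stratum 2 total of 1472 is 368 × 4 without the follow-up allowance; with it, 368 × 4/0.8 = 1840. That is a separate error.)

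**2. Does HR 1.2 give 147?** Schoenfeld: events = 4(2.576 + 1.282)²/(ln 1.2)² = 4 × 14.88/0.03324 ≈ 1,790, or about 895 per group. Freedman's formula gives about 901. One-sided alpha 0.01 gives about 784, and two-sided alpha 0.05 about 632. None is near 147, per group or as a two-group total.

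**3. Power that 147 and 111 give for HR 1.2.**
- 147 per group (294 events): Φ(√(294/4) × 0.1823 − 2.576) ≈ 16%; at two-sided alpha 0.05, about 35%.
- 111 per group (222 events): about 11%, where 80% is stated. About 703 per group would be needed.

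**4. What effect does 147 fit?**
- HR = exp(√(4 × 14.88/294)) ≈ 1.57.
- Difference in means: standardised difference √(2 × 14.88/147) = 0.45, so 1 day requires SD = 1/0.45 ≈ 2.2 days.
- On the means reading, 80% power needs 147 × (2.576 + 0.842)²/(2.576 + 1.282)² ≈ 115.4, so 116, not 111. For a fixed effect this ratio depends only on alpha, so the HR 1.57 reading does not give 111 either.

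**5. Are 1 day and HR 1.2 the same effect?** Only as an illustration: with exponential durations, 1 day at HR 1.2 means 6 against 5 days, with SD about 5.5. Then n = 2 × 14.88 × 5.5² ≈ 900 per group, again about six times 147.

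**6. Consequence if HR 1.2 is the target (two-sided alpha 0.01).**

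| Scenario | Infected per group | Power |
|---|---|---|
| Strata 1 and 3 at 1130 and 1225 | 147 each | 16% |
| Stratum 2 at 1472 as printed | 368 × 0.8 × 0.40 = 118 | 12% |
| Three strata combined at those totals | 147 + 118 + 147 = 412 | 52% |
| Stratum 1 at 4,900 | 980 × 0.65 = 637 | 75% |
| Stratum 2 at 4,900 | 980 × 0.40 = 392 | 49% |
| Stratum 3 at 4,900 | 980 × 0.60 = 588 | 71% |
| Three strata combined at 4,900 each | 1,617 | above 99% |

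For 90% power within each stratum, 895 infected per group would mean about 6,885, 11,190 and 7,460 randomised, or 25,535 in all.

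**The case against.** The strongest defence is that 147 came from a comparison of means and the bracketed hazard ratio is a loose gloss. The primary outcome is a number of days, the 1-day difference comes first in the sentence, and section 2.7.2 foresees negative binomial and mixed models rather than a survival analysis. This stands to the extent that a reader might infer that every revised figure overstates power, and the documents do not support that: it follows only if HR 1.2 is the operative target. The defence does not rescue the text, though. The printed HR would then be wrong, the calculation would rest on an unstated SD, and 111 would remain unexplained.

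The power figures above are also log-rank approximations. The outcome is total days over 6 months, possibly across several infections, and the planned analysis is not restricted to infected people. They test the stated inputs; they are not the trial's actual power.

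Two further inferences are tempting and unsupported. One is that strata will stop recruiting at 1130, 1472 or 1225: no section sets these as stops, the target remains up to 15,000, and section 1.3 assesses impact overall as well as by subgroup. The other is that 147 caused the fall from 4,900 per stratum: both old and new sizes use 147, and the fall comes from infection rates well above 15%. Holding the other assumptions fixed is openly disclosed.

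**Conclusion.** The point holds as an internal inconsistency. Either the HR of 1.2 or the stated power is wrong in section 2.6, by a factor of about six in infected people per group (895 against 147), and no reading tried at alpha 0.01 yields both 147 and 111. The figures 226/1130, 368/1472, 245/1225, 171/855 and 1388 inherit this.

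Whether power is overstated depends on which effect is meant. If HR 1.2, the figures in step 6 apply, and the harm is confined to stratum-level power claims and the revised totals, because the combined comparison at 4,900 per stratum keeps more than 99%. If 1 day with SD about 2.2, the 90% can stand once that SD is stated and justified, but the HR and the 80% figure need correcting. These conclusions assume a two-sided pairwise test and one event per infected person; the one-sided version changes the size of the gap but not its existence.

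**What to change.** In section 2.6, take one of two routes:

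- Replace HR 1.2 with the effect that 147 detects: an HR of about 1.57, or 1 day with the SD stated. Check that SD against blinded illness-day data pooled over groups from seasons 1 and 2.
- Keep HR 1.2 and restate the power actually delivered, per stratum and with strata combined.

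Then recompute the revised primary-outcome estimates, including the 80%-power figures based on 111, and state the sidedness of alpha.

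The cost is a few hours of recalculation and a rewritten paragraph. No enrolment beyond the existing maximum is required, provided that lower stratum-level power is accepted if HR 1.2 is kept; 90% in every stratum would not fit within 15,000. The stated power becomes less favourable.

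### The 80%-power figure of 111 per group does not follow from the stated alpha of 0.01 (about 116 is needed), so the totals of 855 and 1388 are about 4% too small

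*Protocol article*

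**What the plan says.** All the relevant text is in section 2.6 (Sample size) of the protocol article.

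- The provisional calculation gives the base case for the primary outcome: "for alpha of 0.01 and 90% power, we estimated we would require 147 individuals per group". The effect is described as follows: "To detect a 1-day difference among individuals having an infection (hazard ratio 1.2"). No standard deviation is given, and the text does not say whether alpha is one- or two-sided. An alpha of 0.05 appears only for the incidence of infections, which is a secondary outcome.
- The revised estimate for stratum 1 keeps that base: "Based on the original number per group of 147 (i.e. changing no other assumptions"). It then lowers the power: "For 80% power, based on the original assumptions, we would require 111 per group". The result is carried forward: "If 65% get an infection, then we would need 111/0.65 = 171 per group", and then "For 4 groups with 80% follow up we would require 855 participants".
- The revised estimate for stratum 2 uses an infection rate of 40% and says: "For 80% power, we would require 1388 participants". The per-group figure is not shown there, but 1388 is what 111 produces (see the working).

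**The concern.** The text says that the 80% figure rests on the same assumptions as the 90% figure. Alpha and effect are then fixed, only power moves, and the ratio of the two sample sizes is determined whatever the effect size was. The stated ratio, 111/147 = 0.755, is lower than alpha 0.01 allows. It lies close to the ratio for a two-sided alpha of 0.05.

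If so, the 80% and 90% figures quoted side by side for strata 1 and 2 are not on the same basis, and the 80% totals do not deliver the power stated for them. A reader choosing between the two power levels would see a slightly larger saving than really exists.

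**Working it through.** **Inputs** (section 2.6, except where noted)
- 147 infected individuals per group at 90% power, alpha 0.01.
- 111 infected individuals per group at 80% power, same assumptions.
- Infection rates: 65% in stratum 1, 40% in stratum 2.
- Four groups and 80% follow-up, so the total is the per-group number × 4/0.8, that is × 5.
- Assumption: two-sided test (not stated for the primary outcome).

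**Step 1. Reproduce the plan's totals from 111.**
- Stratum 1: 111/0.65 = 170.8, so 171 per group; 171 × 5 = 855. Matches.
- Stratum 2: 111/0.40 = 277.5; 277.5 × 5 = 1387.5, so 1388. Matches.

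Both totals follow correctly from 111. There is one wrong input, not three separate slips.

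**Step 2. Scale 147 from 90% to 80% power.** For a fixed effect, n is proportional to (z_alpha + z_power)², so

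n(80%) = 147 × [(z_alpha + 0.842)/(z_alpha + 1.282)]².

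| Alpha | z_alpha | Ratio | n at 80% power | Rounded up |
|---|---|---|---|---|
| 0.01 two-sided | 2.576 | 0.785 | 115.4 | 116 |
| 0.01 one-sided | 2.326 | 0.771 | 113.3 | 114 |
| 0.05 two-sided | 1.960 | 0.747 | 109.8 | 110 |
| 0.05 one-sided | 1.645 | 0.722 | 106.1 | 107 |

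A t-test version anchored on 147 at 90% power gives 116 at two-sided alpha 0.01, and exactly 111 at two-sided alpha 0.05. Solving the ratio 111/147 for alpha gives about 0.038 two-sided, a value the protocol uses nowhere.

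**Step 3. Is two-sided the right reading?** The incidence figures in the same section can be recomputed at alpha 0.05. Two-sided gives 227, 170, 477, 356 and 231, against the stated 227, 170, 476, 356 and 231. One-sided gives 185, 134, 388, 281 and 188. Those calculations were therefore two-sided. They concern a different outcome, so this supports the two-sided reading of the primary calculation but does not prove it.

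**Step 4. Power with 111 per group** (two-sided alpha 0.01, anchored on 147):

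z_power = √(111/147) × (2.576 + 1.282) − 2.576 = 0.869 × 3.857 − 2.576 = 0.776, so power = 78.1%. (The sum is 3.857 with unrounded quantiles.)

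**Step 5. Totals with 116 per group.**
- Stratum 1: 116/0.65 = 178.5, so 179 per group; 179 × 5 = 895. The stated 855 is 40 short (4.5%).
- Stratum 2: 116/0.40 = 290 per group; 290 × 5 = 1450. The stated 1388 is 62 short (4.3%).

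With the unrounded 115.4 the totals are about 888 and 1443, and the stated figures are 3.7% to 3.8% low.

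**The case against.** Nobody can show that 111 is right, but four points limit the finding.

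1. **Sidedness is not stated.** At one-sided alpha 0.01 the requirement is 114, and 111 gives 79.1% power. This stands as a caveat: the gap shrinks to 3 per group, but 111 is still not reproduced.
2. **The test is not stated either.** Section 2.7.2 says that the primary-outcome analysis compares all groups. If the calculation were for a global test with 3 degrees of freedom at alpha 0.01, 147 would scale to about 118. This makes 116 the answer for a two-group comparison rather than the only possible answer. It moves further from 111, not closer.
3. **The practical effect is slight.** Two points of power is less than the uncertainty in the infection rates. In stratum 1 the plan uses 65%, a lower confidence limit, where 71% was observed. At 71%, 116/0.71 × 5 is about 817, below the stated 855, so that margin absorbs the shortfall. In stratum 2 the observed rate of about 40% is used directly, so there is no such margin.
4. **Larger problems lie nearby.** A hazard ratio of 1.2 at two-sided alpha 0.01 and 90% power needs about 1791 events in a two-group comparison (Schoenfeld), or about 896 per group, so 147 does not come from that hazard ratio. The 90%-power total for stratum 2, 1472, is 368 × 4 without the follow-up allowance; with it, the total is 368 × 5 = 1840. Both matter more than this point. Neither makes 111 follow from 147, and correcting 1472 alone would leave 1388 wrong.

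The protocol also does not label the 80% figures as recruitment targets, so nothing here shows that recruitment was cut to them.

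**Conclusion.** The concern holds. Taking 147 as given, alpha 0.01 and 80% power require 116 per group for a two-sided two-group comparison, 114 if one-sided and about 118 for a global four-group test. None of these gives 111. On the two-sided reading, 111 per group has about 78% power, and the totals of 855 and 1388 are about 4% too small.

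The result does not depend on the effect size or the standard deviation, since both cancel. It does depend on the protocol's own statement that the original assumptions were kept. That an alpha of 0.05 was used by mistake is a plausible explanation, but an inference. The point is minor: it is a stated number that does not follow from its stated inputs, and it does not threaten the design.

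**What to change.** In section 2.6, for the two-sided two-group comparison, change three figures: 111 to 116, 855 to 895 and 1388 to 1450. The intermediate 171 per group in stratum 1 becomes 179. Alternatively, if the 80% figures were meant to use another alpha, say so and remove the statement that they rest on the original assumptions. In either case, state the sidedness and the test behind both 147 and the 80% figure.

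Do this together with the correction of the base figure of 147, because any change there replaces these numbers as well; the same scaling factor of 0.785 would then apply to the new base. The cost is a few edited numbers, slightly less favourable, with no change to the conduct of the trial.

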#### 2.5.3 Randomisation

The randomisation process (1:1:1:1) for this trial will be fully automated. The Immune Defence website software will generate a randomisation sequence and computer algorithm to block randomise participants to the 4 trial groups. As randomisation is automated, the sequence will be concealed from the trial team. Patients will be stratified on the basis of whether they are in a higher risk group (over 65 and/or having comorbid condition) and whether or not they have recurrent RTIs (≥3 in the last year) to three strata: stratum 1 (recurrence, no risk factors); stratum 2 (risk factors, no recurrence); stratum 3 (risk factors plus recurrence).

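### The stratum 2 total of 1472 for 90% power leaves out the 80% follow-up allowance it claims; the total should be 1840, and 1472 gives about 81% power

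*Protocol article*

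**What the plan says.** Section 2.6 of the protocol article starts from infected participants. It says that "for alpha of 0.01 and 90% power, we estimated we would require 147 individuals per group". That number is divided by the expected proportion infected, multiplied by four groups and inflated for 80% follow-up. With the provisional 15% infected this gives 980 per group and 4900 in total.

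The revised estimates for the primary outcome repeat the calculation by stratum, using infection rates from the first two seasons. For stratum 2, "the observed infection rate has been around 40% compared to our assumption of 15"%, so "we would require 147/0.40 = 368 per group". The text continues: "With 4 groups and 80% follow up this gives a total of 1472 for 90% power". The next sentence gives the lower-power alternative: "For 80% power, we would require 1388 participants".

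**The concern.** The sentence with 1472 says it allows for both four groups and 80% follow-up. The product of 368 and 4 is exactly 1472, which leaves no room for any follow-up allowance.

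The two stratum 2 figures also do not fit together. As printed, moving from 80% to 90% power costs 84 people (1388 to 1472), a rise of 6%. In stratum 1 the same step costs 32% (855 to 1130). The infected numbers behind both strata are the same, 111 and 147, so the proportional step should be about the same.

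What is at stake is the power claimed for the primary outcome in one of the three strata in which section 1.3 commits to assessing impact. Anyone judging recruitment in stratum 2 against 1472 would believe that 90% power had been secured when the design gives little more than the 80% case.

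**Working it through.** **Inputs, all from the protocol article**
- Infected participants needed per group: 147 for 90% power at alpha 0.01 (section 2.6, provisional calculation); 111 for 80% power (section 2.6, revised estimates, stratum 1).
- Proportion infected in stratum 2: 40% (section 2.6, revised estimates).
- Follow-up: 80%.
- Groups: four, allocated 1:1:1:1 (section 2.5.3).

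**Step 1. Reproduce the printed figure**
- Per group: 147/0.40 = 367.5, rounded to 368.
- Four groups: 368 × 4 = 1472. This is the printed total, before any allowance for follow-up.
- With the allowance: 1472/0.80 = 1840 (367.5 × 4/0.80 = 1837.5 if 367.5 is not rounded first).
- Inflating by multiplication instead, 1472 × 1.2 = 1766, does not give 1472 either.
- To reach 1472 with the allowance included, the infection rate would have to be 147 × 4/0.80/1472 = 0.499, about 50%. Otherwise follow-up would have to be 100%. The text states neither.

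**Step 2. Check the convention against every other total in section 2.6**

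| Figure | Calculation | Result | Printed |
|---|---|---|---|
| Provisional | 980 × 4/0.80 | 4900 | 4900 |
| Stratum 1, 90% | 226 × 4/0.80 | 1130 | 1130 |
| Stratum 1, 80% | 171 × 4/0.80 | 855 | 855 |
| **Stratum 2, 90%** | **368 × 4/0.80** | **1840** | **1472** |
| Stratum 2, 80% | (111/0.40) × 4/0.80 | 1387.5 | 1388 |
| Stratum 3 | 245 × 4/0.80 | 1225 | 1225 |
| Incidence, stratum 1, 90% | 227 × 4/0.80 | 1135 | 1135 |
| Incidence, stratum 1, 80% | 170 × 4/0.80 | 850 | 850 |
| Incidence, stratum 2, 90% | 476 × 4/0.80 | 2380 | 2380 |
| Incidence, stratum 2, 80% | 356 × 4/0.80 | 1780 | 1780 |
| Incidence, stratum 3 | 231 × 4/0.80 | 1155 | 1155 |

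Ten of the eleven totals divide by 0.80. Only 1472 does not.

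**Step 3. Check by ratio**
- Required: 147/111 = 1.32.
- Stratum 1 as printed: 1130/855 = 1.32.
- Stratum 2 as printed: 1472/1388 = 1.06.
- Stratum 2 corrected: 1840/1388 = 1.33. The small difference from 1.32 is rounding.

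**Step 4. Power at 1472**
- Followed up per group: 1472 × 0.80/4 = 294.4.
- Infected among them: 294.4 × 0.40 = 117.8, against 147 required.
- Taking 147 as the number that gives 90% power, and alpha 0.01 as two-sided (z = 2.576, with z = 1.282 for 90% power):
  Φ[(2.576 + 1.282) × √(117.8/147) − 2.576] = Φ[3.857 × 0.895 − 2.576] = Φ(0.877) = 0.81.
- Other readings: 80.8% with a t-test, 81.7% with one-sided alpha 0.01, and 82.7% with two-sided alpha 0.05. Linear interpolation between the article's own 111 (80%) and 147 (90%) gives 80 + 10 × (117.8 − 111)/36 = 81.9%.

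**The case against.** The arithmetic itself leaves little to argue about. The stronger reply concerns consequence.

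- **1472 is not stated as a recruitment target.** The recruitment figures in the article are 14,700 and up to 15,000 overall; the stratum figures are presented as estimates of what is required. This stands. No passage says that stratum 2 stops at 1472.
- **Larger stratum 2 numbers appear nearby.** For incidence of infection, section 2.6 gives 2380 for 90% power and 1780 for 80%. Recruiting to 2380 would cover the corrected 1840. Recruiting to 1780 would miss it by 60, about 3%. This also stands, but those figures serve a secondary outcome and do not correct the primary one. The slip also hides the fact that 1780 does not quite cover 90% power on the primary outcome; against 1472 it seems to do so easily.
- **The main comparison is not by stratum.** Section 2.7.2 puts the primary analysis at 6 months across all groups, with subgroup estimates in addition. An error in one stratum's figure leaves the overall comparison's power unchanged. That is correct and limits the reach of the point.
- **The 81% is not the article's own number.** The article does not give sidedness, and scaling from 147 at two-sided alpha 0.01 would imply about 115 infected per group for 80% power, slightly more than the printed 111. So 81% should carry its assumption. The readings above all fall between about 81% and 83%, far nearer to 80% than to 90%.

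Section 2.6 also says that the calculations will be updated when the SAP is drafted. The figure at issue is in the revised estimates, so that statement does not repair it.

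**Conclusion.** The concern holds. The total of 1472 is the uninflated product of 368 and 4, although its sentence says that follow-up is included. The correct total on the article's own inputs is 1840 (1838 without intermediate rounding), a difference of 368 participants, or 20% of the correct figure. This rests only on the printed 147, 40%, four groups and 80% follow-up, and needs no assumption about alpha or sidedness.

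Power at 1472 is about 81% instead of 90%, taking 147 for 90% power as given and assuming two-sided alpha 0.01. The step from 80% to 90% power in stratum 2 costs about 452 participants (1840 − 1388), not 84. If the 90%-power figures are added over strata, a sum the article does not print, the result is 1130 + 1840 + 1225 = 4195 and not 3827.

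The practical effect depends on recruitment. If stratum 2 reaches 1840 or more, and the 40% and 80% assumptions hold, the intended power is met. The statement that 1472 gives 90% power is wrong whatever number is recruited.

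**What to change.** In section 2.6, revised estimates for the primary outcome, stratum 2, replace 1472 with 1840 for 90% power. Alternatively, keep 1472 and state that it gives about 81% power, with the alpha and sidedness assumed. Carry the corrected figure into the SAP and into any stratum-level recruitment tracking, and check whether any decision on stratum 2 recruitment relied on 1472.

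The cost is one corrected number, with no change to design or analysis. If stratum 2 finishes below 1840 and recruitment is not extended, report the power that the achieved number supports.
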